### Primary Outcome

The primary outcome will be progression in ADT use (as documented in the EMR) during the 12-month study period. For both intervention and control centers, a participant’s baseline ADT status will be ascertained in the 12-month period before deployment of the BPA intervention. The primary outcome will be defined as positive for an individual if any of the following transitions from the baseline period to the implementation period occur with respect to ADT:

No CGM → CGM.No AID → AID.

The T1DX-QI database includes variables that will be used to evaluate the study outcome (eg, medication list and flowsheet data). We have extensively published on the T1DX-QI data source and its validation, and have used the database for several real-world studies [36-42].

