## Introduction

Over the past decade, continuous advancements in diabetes technologies have helped to ease the burden of diabetes self-management for people with type 1 diabetes (T1D). Continuous glucose monitors (CGM) and automated insulin delivery (AID) systems have not only led to improved quality of life but also better glycemic outcomes and reduced incidence of hospitalizations for severe hypoglycemia and diabetic ketoacidosis (DKA) [1,2]. Given these clinical benefits, the American Diabetes Association now recommends that CGM be considered the standard of care for all people with T1D and that AID systems be recommended to people with T1D who are capable of safely using them [3].

Despite proven clinical benefits, racial inequities in the use of advanced diabetes technologies (ADTs), such as AID systems and CGMs, persist in both children and adults with diabetes [4-8]. Compared with Non-Hispanic White people with T1D, Non-Hispanic Black people with T1D have 1.5% higher glycated hemoglobin (HbA_1c_) levels on average [9] and are more than 3 times as likely to be hospitalized for hypoglycemia or DKA [10,11], yet they are half as likely to be using ADTs [12].

Factors contributing to these disparities include individual barriers like cost concerns, insertion pain, and alarm anxiety [13-16], as well as provider-level barriers such as insufficient knowledge, bias, and clinical decision-making criteria that do not align with current guidelines [17-19]. System-level barriers include insurance coverage issues and complicated processes for obtaining devices [20,21]. For example, a recent 7-year study at a large academic medical center found significantly lower rates of CGM discussions and use among Black people with T1D compared with their White counterparts, even after adjusting for various other factors [6]. In addition, a study by the T1D Exchange Quality Improvement Collaborative(T1DX-QI) highlighted the presence of implicit racial bias in approximately one-third of endocrinologists when prescribing ADTs [19].

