##### BPA Design

Using a rule-based algorithm, the EMR-based BPA will be designed to recommend ADT prescriptions for people with T1D not already using an AID system, and this would also encompass an alert for people not using CGM (and thus not using AID). The specific functionality of the BPA will be guided by the thematic analysis of the stakeholder input obtained in phase 1. The function will generate a BPA if a patient is not using an AID system and will suggest to the provider to discuss and prescribe technologies for using an AID system.

The BPA design will be led by the study organizing committee with direct involvement and support from Epic IT analysts and developers at Johns Hopkins University. Iterative feedback will be obtained from the principal investigators at each of the participating intervention centers during the prototype development. Table 3 outlines the key considerations for the design team. Throughout the design process, Norman’s user-centered design principles will be applied to ensure the BPA is intuitive, user-friendly, and meets the needs of all stakeholders [35].

**Table 3 table3:** Key considerations for best practice advisory (BPA) design team.

Consideration	Descriptions
Stakeholder input	Incorporate thematic analysis of feedback from patients, caregivers, and health care providers.
Algorithm rules	Define criteria for triggering the BPA based on patient EMR^a^ data.
Workflow integration	Ensure BPA integrates seamlessly into the provider’s workflow.
Iterative testing	Conduct iterative testing and refinement based on feedback from pilot implementations.
Setting and restrictions	Consider the setting (ambulatory, inpatient, both) and specific locations such as endocrinology clinics, primary care clinics, or health-system wide.
Location in Epic	Determine the BPA’s location in Epic, such as Windows, BPA Navigator, or Flag in Storyboard.
Active versus passive	Decide between active (windows that appear in the user’s Epic workflow) and passive (appear within assigned locations that fit into the end user’s workflow) BPAs.
Clinician action	Specify actions clinicians can take, such as placing orders or referrals.
Triggering messages	Determine language in the BPA, including potential references to practice guidelines, explain the reason for the BPA, and suggest actions to be taken.
Iterative testing	Conduct iterative testing and refinement based on feedback from pilot implementations.

^a^EMR: electronic medical record.

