### Phase 2: Evaluation (Study Design)

Using a nonrandomized matched pair-intervention design (ie, controlled before-after study), we will compare the use of ADT following the BPA intervention among non-Hispanic Black and Hispanic people with T1D at 7 participating T1DX-QI centers. These will be matched with control non-Hispanic Black and Hispanic people with T1D at nonintervention T1DX-QI centers over a 12-month period. Both control and intervention centers have completed the EMR data mapping to the T1DX-QI, allowing for consistent outcome assessment across both groups. The study will consist of 2 distinct periods:

Baseline period (before): 12 months before deployment of the BPA at the intervention centers.Implementation period (after): 12 months after the deployment of the BPA at the intervention centers.

The before-after matched-pair intervention design allows for a real-world assessment of the BPA’s impact on ADT use while controlling for key confounders. Comparing ADT prescribing before and after BPA implementation within intervention sites and using matched controls from nonintervention centers, the design also accounts for site-specific prescribing patterns and secular trends. This quasi-experimental approach is practical for an EMR-based intervention and minimizes selection bias by matching key clinical and demographic variables.

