**Inclusion criteria**
Age ≥2 yearsA diagnosis of type 1 diabetes (determined using *ICD-10* [*International Statistical Classification of Diseases and Related Health Problems, Tenth Revision*] diagnosis codes [E10.X] and other various discrete data elements, such as flowsheet rows, as mapped by clinical centers to the Type 1 Diabetes Exchange Quality Improvement Collaborative database).Receiving care at one of the seven intervention centers or a matched control center in the Type 1 Diabetes Exchange Quality Improvement Collaborative.Patients with at least one clinical encounter (in-person or video visit) in both the baseline and follow-up periods.Not prescribed an automated insulin delivery system (patients prescribed only continuous glucose monitoring are eligible, provided they are not prescribed an automated insulin delivery system).

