**Exclusion criteria**
People with type 1 diabetes already using an automated insulin delivery at baseline.Pregnant patients.People with type 1 diabetes receiving end-stage kidney disease dialysis.People with type 1 diabetes using hydroxyurea.

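### The plan does not say whether a prescription alone scores as ADT use, and the alert prompts prescribing in the intervention group only

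*Protocol article*

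**What the plan says.** The Primary Outcome section gives the construct: "The primary outcome will be progression in ADT use (as documented in the EMR) during the 12-month study period". A participant is positive on a change from no CGM to CGM, or from no AID to AID, between the baseline and implementation periods. The same section names the database "variables that will be used to evaluate the study outcome (eg, medication list and flowsheet data" as examples. It does not say which source decides, or whether a prescription without other evidence is enough.

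On the intervention, BPA Design says the alert "will suggest to the provider to discuss and prescribe technologies for using an AID system". Table 3 in that section gives the design team the task "Specify actions clinicians can take, such as placing orders or referrals". The Discussion adds that the BPA is built to include actionable recommendations, with prescriptions as the example. The Deployment section adds feedback to clinicians on their compliance, compared with peers.

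Phase 2: Evaluation (Study Design) describes part of the contrast as "Comparing ADT prescribing before and after BPA implementation within intervention sites", although the outcome is defined as use. The same section says both groups share completed EMR data mapping. Primary Outcome points to published validation of the database, and Data Collection lists ADT use among the mapped outcome data.

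**The concern.** A prescription is a step towards use but is not use. The Introduction itself names what lies between them: "System-level barriers include insurance coverage issues and complicated processes for obtaining devices". If the outcome can be met at the prescription step, the trial could report a gain in use that is partly a gain in orders. The shortfall would arise at the step where the target population may be lost.

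The error would not fall equally on the two groups. The alert prompts prescribing, and possibly attention to the device record, at intervention centers only. One scoring rule for everyone then does not protect the comparison, because the intervention changes how often the record is altered in one group. Matching balances baseline covariates and cannot correct recording that changes after deployment. The secondary comparison of ADT use between White and non-White patients would share the problem if it draws on the same fields.

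**Working it through.** The plan has no figure of its own to reproduce here, so the check has two parts: the logic of the text, then an illustration of scale.

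**Logic of the text**
1. The outcome is a recorded transition in ADT status (Primary Outcome).
2. The medication list is one named example of a source (Primary Outcome).
3. The intervention asks for a prescription (BPA Design, Discussion), in one group only.
4. No sentence says that a medication-list entry alone is insufficient.
5. If it is sufficient, and if orders reach that list, an order never followed by a device scores as progression. These are two conditions, and the article confirms neither.
6. Separately, Table 3 bases the alert's trigger on EMR data, so a user whose device was never recorded could also trigger it. If the clinician then corrects the record, the transition rule is met with no new use. That clinicians would do so is also an inference.

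**Scale, part 1: orders against use.** Assume the BPA adds 10 points of orders and 50% to 80% become devices in use. The true gain is then 10 × 0.5 = 5 to 10 × 0.8 = 8 points, reported as 10.

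**Scale, part 2: corrected records.** Assume 2% to 10% of recorded non-users already use a device and the alert gets half of them corrected. The spurious progression is 2 × 0.5 = 1 to 10 × 0.5 = 5 points. The smallest difference considered in the Power section is 5 points.

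**Scale, part 3: chance of a significant result from records alone.** From the documents: control progression 15% and 589 pairs (Power), 3000 intervention patients (Results), 1:4 matching (Control Group). Assumed: no true change in use, two-sided alpha 0.05, independent patients, no center clustering. With d the excess at intervention centers, p1 = 0.15 + d, p2 = 0.15, n2 = k × n1 and p̄ the pooled proportion:

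- SE0 = √[p̄(1 − p̄)(1/n1 + 1/n2)]
- SE1 = √[p1(1 − p1)/n1 + p2(1 − p2)/n2]
- chance = Φ[(d − 1.96 × SE0)/SE1]

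For d = 0.02 with 589 pairs, SE0 = 0.02136 and SE1 = 0.02135, so the chance is Φ[(0.02 − 0.04187)/0.02135] = Φ(−1.02) = 0.15. For d = 0.02 with 3000 against 12,000, SE0 = 0.00737 and SE1 = 0.00759, so it is Φ[(0.02 − 0.01444)/0.00759] = Φ(0.73) = 0.77.

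| Record-only excess | 589 pairs, 1:1 | 3000 patients, 1:4 |
|---|---|---|
| 1 point | 7% | 28% |
| 2 points | 15% | 77% |
| 3 points | 28% | 98% |
| 5 points | 62% | about 100% |

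The planned mixed model has random center effects, and clustering would lower these chances. It would not remove the bias in the estimate.

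**The case against.** The strongest reply is that the article fixes no such rule. The sources are only examples, ADT use is itself a mapped variable, and its derivation may sit in the full protocol or analysis plan. Order placement in Table 3 is still a design question. This stands in part: a reader might infer that orders from the BPA will fill the medication list and be counted as use, and the documents do not say so. It does not dispose of the point. The article names the medication list as a source for use and describes the contrast as one of prescribing, and the safeguards it offers concern ordinary data quality, not recording that the intervention changes in one group.

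A second reply is that unfilled orders also occur in controls, so only the excess matters. That is correct. If the same share of recorded transitions became use in both groups, the ratio of proportions would be unchanged, though the absolute difference would still be overstated. Part 1 of the scale is also an inflated real effect; only part 2 creates an effect from nothing, and it rests on the weaker inference.

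A reader might also infer that the eligibility lines contradict each other, since one requires "Not prescribed an automated insulin delivery system" and the other removes "People with type 1 diabetes already using an automated insulin delivery at baseline". They do not. Both can apply at once, so that an eligible patient is neither prescribed nor using AID.

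Finally, scoring only flowsheet or device fields would not be a clean cure. Flowsheet elements are mapped by each center, completeness may differ across centers, and such a field can be corrected after an alert too. This stands, and it shapes the fix.

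**Conclusion.** The point holds as a conditional one. If a medication-list entry alone can score a transition, the primary outcome could overstate progression in use more at intervention centers than at control centers. The same applies if the alert prompts documentation of earlier use. The documents establish that the medication list is a named source and that the alert prompts prescribing in one group. They do not establish that orders populate that list, that alerts lead to corrected records, or how large either effect would be. The 5-to-8-point and 1-to-5-point ranges and the table rest on assumptions and show sensitivity, not an expected bias. The change should be made because it is cheap and bears on what the trial may conclude, but the text does not show that the result will be wrong.

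**What to change.** 1. State in Primary Outcome whether a prescription alone counts as use, and apply the same rule in both groups and both periods.
2. Report new prescriptions and documented use (flowsheet or device documentation) as separate outcomes.
3. Prespecify a sensitivity analysis of the primary outcome that excludes transitions supported only by a medication-list entry. Where dates are available, it should also count only transitions whose device start falls in the implementation period. An order date would not serve here, because it does not show that a device was obtained.
4. If the medication list remains sufficient for the primary outcome, word the conclusion as progression in ADT prescribing or use.

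The cost is some added derivation and analysis work. Data Collection says the dataset includes dates, but the article names no device start field, so the date restriction may be possible only for some patients. The event rate will be lower in the sensitivity analysis, partly because devices ordered late in the 12 months may not yet be recorded as in use. Flowsheet completeness may be uneven across centers. For these reasons the stricter definition is proposed as a sensitivity analysis and not as a required replacement. Keeping it there also leaves the 15% control rate in the Power section undisturbed.

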### Adverse Events

It is not anticipated that the intervention will pose any additional risk of harm to people with T1D, particularly given the established benefits of AIDs and CGMs in enhancing glycemic control and reducing the risk of hypoglycemia. Nevertheless, the study will closely monitor rates of serious hypoglycemic events and DKA events, using existing data mapped from control and intervention sites to the T1DX-QI database. These rates will be compared between the intervention and control sites to ensure that there are no unexpected or unintended consequences of the intervention on adverse glycemic outcomes.

### Statistical Analysis

#### Data Collection

Currently, more than 102,000 people with T1D have EMR data in the T1DX-QI database. Mapped outcome data include ADT use, HbA_1c_, severe hypoglycemic events, and DKA events, and are automatically transmitted to the T1DX-QI database monthly. Data from all intervention and control sites will be analyzed by the T1DX-QI data coordinating center. All data are anonymized and deidentified to ensure patient privacy. Protected health information is in the form of a limited dataset, which includes dates but excludes any direct identifiers. Medical record numbers are never shared with T1DX. Unique identifiers are created by the hospitals and shared with T1DX for the purpose of longitudinal (encounter-level) data analysis. Results are aggregated, and no encounter-level data are published, further safeguarding participant confidentiality. The data monitoring committee will be composed of the principal investigators from JHU and T1DX-QI, along with biostatisticians, and will operate independently from the sponsor. Members of the data monitoring committee will have access to the final trial dataset.

#### Power

This study is powered to detect a between-group difference of 15% in the proportion of patients in the intervention and control groups meeting the primary endpoint. The matched-pair control assessment of 15% progression in ADT use is estimated from T1DX-QI data over a previous 12-month period. The largest sample size necessary for 90% power if the absolute difference in the proportion of ADT progression is only 5% (relative increase of 25%) is 589 matched pairs. If possible, we will attempt to match intervention to control patients in a 1:2 fashion with 2 matched controls per intervention patient. An interim analysis of the intervention group event rate may be conducted to inform whether additional matched pairs are needed.

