### Analysis

#### Phase 1

For survey data, Likert scale responses will be coded numerically for qualitative analysis. Descriptive statistics will be calculated to summarize the data, and differences between groups (ie, based on demographic variables) will be explored. For the structured interviews and focus groups, a thematic approach will be used to identify, analyze, and report patterns with the qualitative data. NVivo software will be used, which provides features for coding, organizing, and visualizing data [43]. Both deductive and inductive coding methodologies will be used to link similar codes to broader themes based on significant phrases, concepts, and ideas present in the transcripts [44]. Themes will be reviewed and refined through discussions among the research team to ensure consistency and reliability.

#### Phase 2

The primary outcome will evaluate the impact of the BPA intervention on patients’ progression of ADT use using a generalized linear mixed model to account for matched pairs and random center effects. The model will be adjusted for the number of encounters and other possible confounders not already matched.

The secondary outcome analyses will compare differences in ADT use between non-White and White people with T1D in the intervention and control groups. Additional secondary and exploratory outcomes will be assessed using the appropriate statistical model for the outcome adjusting for patient- and center-level confounders. Exploratory analysis assessing pediatric and adult centers separately will be performed.

In cases where ADT is not prescribed by the provider, we will explore the reasons why, and why the diabetes technology was not offered or accepted by patients. We will quantify the BPA responses as provider-led or patient-led reasons for not advancing ADT use. We will perform multivariable logistic regression analysis to evaluate whether patient characteristics (demographics, race, ethnicity, diabetes characteristics, and complications) are associated with the reasons that technologies are not offered or declined.

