## Results

The BPA-TECH study funding was finalized in April 2024. Data collection for the phase 1 qualitative component of this study began in August 2024 and is expected to be completed around July 2025. Phase 2 will commence with the deployment of the BPA, followed by a 12-month evaluation period that is expected to conclude around July 2026. We estimate evaluating data from 3000 eligible people with T1D across the 7 clinical centers and 15,000 possible matched controls across 41 centers.

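### The 90% power claimed for a 5-point difference counts matched pairs as independent, although the advisory is switched on by center at only 7 centers; it fails once the residual ICC exceeds about 0.007

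*Protocol article*

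**What the plan says.** The Power section gives a headline target: "This study is powered to detect a between-group difference of 15% in the proportion of patients". It then gives its only sample size, for a smaller effect: "The largest sample size necessary for 90% power if the absolute difference in the proportion of ADT progression is only 5" percentage points, described there as a 25% relative increase, "is 589 matched pairs". The control rate is sourced as follows: "The matched-pair control assessment of 15% progression in ADT use is estimated from T1DX-QI data".

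The section states no ICC, design effect or number of centers. Its routes to more power are two matched controls per intervention patient and, after a possible interim look at the intervention event rate, further pairs.

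The design sections describe assignment by center. The Introduction calls the intervention center-wide at 7 centers. The Intervention Group section places every eligible patient at those centers in the intervention arm, and the Control Group section draws controls only from other centers. The Results section expects "3000 eligible people with T1D across the 7 clinical centers and 15,000 possible matched controls across 41 centers". The Phase 2 analysis is to be done "using a generalized linear mixed model to account for matched pairs and random center effects".

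**The concern.** Exposure to the advisory never varies within a center, so any difference between centers in 12-month progression goes straight into the error of the treatment comparison. The primary model allows for this; the power statement does not. The two therefore describe different designs.

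The cost falls on interpretation. A null result could be read as coming from a trial with 90% power for 5 points when it had much less. The interim look would also steer effort toward more pairs when the number of intervention centers may be the limit.

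**Working it through.** **Inputs.** From the protocol: control rate 15%; difference 5 points (so 20%) or 15 points (so 30%); 90% power; 7 and 41 centers; 3,000 intervention patients; 1:4 matching in the Control Group section, so 4 × 3,000 = 12,000 controls. Assumed because not stated: two-sided 0.05 (z = 1.960, and 1.282 for 90% power), equal center sizes, residual ICC 0.005 to 0.05, normal approximation.

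**1. The plan's figure of 589.**
- Unpaired, 1:1: n = [1.960·√(2 × 0.175 × 0.825) + 1.282·√(0.1275 + 0.16)]² / 0.05² = 1,212 per arm.
- McNemar: n = [1.960·√ψ + 1.282·√(ψ − 0.05²)]² / 0.05², where ψ is the discordant proportion. Independent pairs have ψ = 0.15 × 0.80 + 0.85 × 0.20 = 0.29, which gives 1,215 pairs.
- The formula returns 589 only at ψ of about 0.141, a within-pair correlation of about 0.52. Neither value is stated.

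So 589 is about half the independent-patient number and cannot contain an allowance for clustering.

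**2. Clustered variance, full sample.** Patients per center: 3,000/7 = 428.6 and 12,000/41 = 292.7.

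Var = 0.16·[1 + 427.6·ICC]/3,000 + 0.1275·[1 + 291.7·ICC]/12,000; power = Φ(0.05/√Var − 1.960).

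At ICC 0.01 the design effects are 5.28 and 3.92, so 3,000 patients count as about 569 and 12,000 as about 3,064. Var = 0.000281 + 0.000042 = 0.000323, SE = 0.0180, z = 2.78, power 79%. The intervention arm supplies 0.000281/0.000323 = 87% of the variance.

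| Residual ICC | Power, 15% vs 20% | Difference detectable with 90% power |
|---|---|---|
| 0 | over 99% | 2.5 points |
| 0.005 | 95% | 4.5 points |
| 0.01 | 79% | 5.9 points |
| 0.02 | 54% | 8.2 points |
| 0.05 | 27% | 13.3 points |

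**3. Where 90% is lost.** 90% power requires Var ≤ (0.05/3.242)² = 0.000238. With 3,000 and 12,000 patients this is reached at ICC 0.0067 (0.0055 with 1:1 matching).

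With unlimited patients in the same centers, Var tends to ICC·(0.16/7 + 0.1275/41) = 0.02597·ICC. The limit is then ICC 0.000238/0.02597 = 0.0092. At ICC 0.01 even unlimited patients give 87%.

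**4. Headline target, 15% vs 30%.** Replace 0.16 by 0.30 × 0.70 = 0.21. At ICC 0.05: SE 0.0416, z = 3.60, power 95%. At ICC 0.10: SE 0.0582, z = 2.58, power 73%.

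**5. Granting the pairing implied by 589.** Subtract 2 × 0.52 × √(0.16 × 0.1275)/n from the 1:1 variance. With 3,000 pairs, power at ICC 0.01 is 82%, and 90% is lost at ICC 0.0074. With 589 pairs, power is 90% at ICC 0, 75% at 0.005 and 62% at 0.01.

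**The case against.** - **The ICC is assumed.** This stands. The protocol gives none, and at ICC 0.005 the full sample still has 95% power. For scale, ICC 0.01 at a 15% rate is a between-center SD of √(0.01 × 0.1275), about 3.6 points. The conclusion has to be given as a range.
- **Matching may absorb center differences.** The propensity model includes clinic size, staffing, location and historical device use. This may lower the residual ICC. It is not shown to remove it, and the primary model keeps random center effects.
- **The headline target survives.** A reader might infer that the whole study is underpowered. The documents do not support that: the 15-point target keeps 95% power at ICC 0.05. The shortfall concerns the 5-point scenario.
- **More pairs do help at low ICC.** A reader might infer that added pairs can never restore power. That is true only above an ICC of about 0.009.
- **The shortfall at 589 pairs is not all clustering.** Under an unpaired variance, 589 per arm gives SE = √(0.2875/589) = 0.0221, z = 2.26 and 62% power at ICC 0. The gap between 62% and 90% comes from the unstated discordance assumption. The full-sample rows isolate the effect of clustering.
- **The analysis already handles clustering.** This stands. The point concerns the power claim, not the validity of the primary model.

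**Conclusion.** The statement that 589 pairs give 90% power for 5 points does not match the stated design. Even with the full expected sample, 90% power for 15% versus 20% holds only if the residual between-center ICC stays below about 0.007. How far power falls beyond that depends on an ICC the documents do not supply, on equal center sizes and on a normal approximation. Unequal sizes make it worse: with a size coefficient of variation of 0.5, power at ICC 0.01 is 72%. The relative increase of 25% in the same sentence would instead imply 20% versus 25%; 5 points on 15% is 33%. On the 20% base, power at ICC 0.01 is 68% to 73%, depending on the matching ratio.

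**What to change.** Restate the Power section as a cluster calculation with 7 versus 41 centers and the expected full sample. Estimate the residual between-center ICC of 12-month progression, after the planned matching covariates, from the same network data that gave the 15% rate. Report the 90%-power detectable difference over a range around that estimate, and give power for the 15-point target separately. Withdraw the claim that 589 pairs give 90% power for 5 points.

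The cost is one query of existing data and revised wording. The design, the primary model and the number of patients stay as they are. The downside is a larger stated detectable difference.

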**Results:**

This 3-year study began in July 2024, with data collection from key stakeholders for phase 1 qualitative research beginning in August 2024. For phase 2, we estimate approximately 3000 eligible non-Hispanic Black and Hispanic people with type 1 diabetes at the intervention centers and 15,000 matched controls. Data on ADT use, glycated hemoglobin (HbA_1c_), severe hypoglycemic events, and diabetes ketoacidosis events will be collected via the T1DX-QI coordinating center. The study is powered to detect a between-group difference of 15% in the proportion of patients in the intervention and control groups in meeting the primary endpoint. We anticipate the completion of this study by May 2027.

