Propensity scores will be estimated using logistic regression, where the outcome variable is the likelihood of receiving the BPA intervention. The model will include the identified patient-level and clinical center–level covariates as predictors. The estimated propensity score represents the predicted probability that a given patient would receive the BPA based on their covariate profile. Patients in the intervention group will be matched to patients in the control group using a 1:4 matching ratio. Nearest neighbor matching without replacement will be used, ensuring that each control patient is only matched once. The matching process will aim to minimize the distance between propensity scores of matched pairs, thus creating comparable groups. The quality of the matching process will be assessed by comparing the distribution of covariates between the matched intervention and control groups. Standardized mean differences will be calculated for each covariate to ensure balance, with a standardized mean difference of less than 0.1 indicating adequate balance. In addition, a visual inspection of propensity score distributions before and after matching will be conducted to confirm the success of the matching process.

To assess the robustness of the results, sensitivity analyses will be performed using different matching algorithms (eg, caliper matching and kernel matching) and varying the matching ratio (eg, 1:3). In addition, the impact of imputation on the results will be examined by comparing outcomes using datasets with and without imputed values.

For nonstatic matching variables (eg, laboratory results), the last available result in the baseline period of 12 months before the BPA deployment date in the intervention centers will be used.

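### The 589 matched pairs cannot be reproduced from the printed inputs, and a 5-point rise on the stated 15% control rate is a 33% relative increase, not 25%

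*Protocol article*

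**What the plan says.** All the figures are in the Power section of the protocol article.

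- Headline target: "This study is powered to detect a between-group difference of 15% in the proportion of patients in the intervention and control groups", counting those who reach the primary outcome. The abstract repeats it.
- Control rate: "The matched-pair control assessment of 15% progression in ADT use is estimated from T1DX-QI data over a previous 12-month period".
- Sample size: the number is introduced as "The largest sample size necessary for 90% power". Its condition and its value come next in the same sentence: "the absolute difference in the proportion of ADT progression is only 5% (relative increase of 25%) is 589 matched pairs".
- Matching ratio: 589 is expressed in pairs, so 1:1. The next sentence sets a further aim, where feasible: "we will attempt to match intervention to control patients in a 1:2 fashion with 2 matched controls per intervention patient". The Control Group section instead says "Patients in the intervention group will be matched to patients in the control group using a 1:4 matching ratio".
- Interim look: the section allows a check of the intervention group's event rate to judge whether more matched pairs are needed.

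The primary analysis is described as "using a generalized linear mixed model to account for matched pairs and random center effects". The Power section gives no alpha, sidedness, discordant-pair proportion or within-pair correlation. The Results section expects about 3,000 intervention patients and 15,000 possible controls.

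**The concern.** The 15% control rate, the 5-point difference and the 25% relative increase cannot all be right. A reader cannot tell whether the calculation compared 15% with 20% or 20% with 25%. On either reading, 589 is less than half of what a standard calculation gives for two unrelated patients per pair.

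589 is the only sample size in the article, so it is the natural benchmark for the interim question of whether to add matched pairs. It also shapes how a null result would be read: a reader would credit 589 pairs with 90% power to exclude a 5-point effect. If the true requirement is about twice that, both uses go wrong.

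**Working it through.** **Inputs.** Control rate 15% (Power section), or 20% (implied by 5 points being 25% relative); difference d = 0.05; power 90%. Assumed because not printed: two-sided alpha 0.05, and a range of within-pair correlation phi. Hence z_a = 1.960 and z_b = 1.2816.

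**1. Relative increase.** 5/15 = 33%; 5/20 = 25%. Taking 25% of 15% gives 3.75 points, not 5.

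**2. Trying to reproduce 589 with uncorrelated 1:1 groups.** With pbar the mean of the two rates,

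n = [z_a·sqrt(2·pbar·(1−pbar)) + z_b·sqrt(p0(1−p0) + p1(1−p1))]² / d²

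- 15% vs 20% (pbar = 0.175): n = 1,212
- 20% vs 25% (pbar = 0.225): n = 1,464
- One-sided 0.05: 988 and 1,193

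None is near 589.

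**3. Paired (McNemar) form.** With pd the proportion of discordant pairs,

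n = [z_a·sqrt(pd) + z_b·sqrt(pd − d²)]² / d²

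pd = p0 + p1 − 2·p11, where p11 = p0·p1 + phi·sqrt(p0(1−p0)·p1(1−p1))

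At phi = 0, pd is 0.29 (15% vs 20%) and 0.35 (20% vs 25%), giving 1,215 and 1,467 pairs, in line with step 2. Raising phi lowers the requirement:

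| phi | pairs, 15 vs 20% | power at 589 | pairs, 20 vs 25% | power at 589 |
|---|---|---|---|---|
| 0 | 1,215 | 62% | 1,467 | 54% |
| 0.2 | 975 | 71% | 1,176 | 63% |
| 0.3 | 855 | 77% | 1,031 | 69% |
| 0.5 | 615 | 89% | 739 | 82% |
| 0.52 | 591 | 90% | 710 | 84% |
| 0.60 | 495 | 94% | 594 | 90% |

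Setting pd = 0.141 returns 589. That corresponds to phi of about 0.52 for 15% vs 20%, or about 0.60 for 20% vs 25%.

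**4. What phi = 0.52 means at 15% vs 20%.** sqrt(0.15·0.85·0.20·0.80) = 0.1428, so p11 = 0.03 + 0.52·0.1428 = 0.1043. An intervention patient would progress with probability 0.1043/0.15 = 70% if the matched control did, and (0.20 − 0.1043)/0.85 = 11% if not.

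**5. Do the other ratios explain 589?** The same unpaired formula with k controls per intervention patient (two-sided 0.05, 90% power, uncorrelated) gives these numbers of intervention patients:

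- 1:2: about 901 (15% vs 20%) or 1,091 (20% vs 25%)
- 1:4: about 745 or 905

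With 589 intervention patients, power would be 75% or 67% at 1:2, and 82.5% or 75% at 1:4. Neither ratio gives 90%.

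**6. The 15-point target.** 15% vs 30% needs about 161 per group (164 pairs by McNemar at phi = 0), so any sample sized for 5 points covers it.

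**7. Against the expected sample.** With 3,000 uncorrelated 1:1 pairs and no clustering, power for 5 points is above 99% at either control rate.

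**The case against.** The strongest defence is that 589 is given in matched pairs, and a paired calculation depends on a discordance that a journal article may leave to the full protocol or analysis plan. With about 14% discordant pairs the formula returns 589, so the number is not arithmetically impossible. That stands, and it means that 62% or 54% power cannot be stated as fact: it assumes two-sided 0.05 and uncorrelated 1:1 pairs. But the defence needs a correlation of 0.52 to 0.60 between different people at different centers, matched on a propensity score for receiving the advisory. The article does match on many patient and center characteristics, but it offers no figure for the dependence this creates. The defence also leaves the clash between 25% and 33% untouched.

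Three stronger readings are tempting, and the article does not support them.

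- *The 15% and 5% differences contradict each other.* The wording around 5 points presents it as the least favourable case, so the two can be read as a target and a conservative scenario. That 15% is both control rate and target may suggest a mix-up, but nothing shows one.
- *The abstract's 15% is wrong.* It agrees with the first sentence of the Power section.
- *The trial is underpowered.* Nothing makes 589 a cap or a stopping point for matching, and about 3,000 intervention patients are expected.

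**Conclusion.** The point holds as an error in the stated sample size. The inconsistency between 15%, 5 points and 25% needs no assumption. That 589 cannot be reproduced rests on two-sided alpha 0.05 and on weak or no within-pair correlation. Under those conditions the 1:1 requirement is understated by a factor of 1,212/589 = 2.1 or 1,464/589 = 2.5. A correlation of 0.2 narrows the gap but does not close it, and neither matching ratio named in the article closes it.

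The consequence is limited. The expected 3,000 intervention patients are 2.5 times 1,212 and 2.0 times 1,464. All of these numbers ignore center clustering, which this check did not size. The harm would come from using 589 as the benchmark for adding pairs, or from reading a null result as if 589 pairs carried 90% power.

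**What to change.** In the Power section:

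1. State one control rate, with the absolute and relative differences that follow from it: 15% to 20% is 33% relative, 20% to 25% is 25%.
2. State alpha, sidedness and a single matching ratio that agrees with the Control Group section.
3. Restate the required number without relying on strong within-pair correlation. With two-sided 0.05, for 15% vs 20% or 20% vs 25% respectively, this is about 1,212 or 1,464 pairs at 1:1, 901 or 1,091 intervention patients at 1:2, and 745 or 905 at 1:4, all before center clustering. Alternatively, keep 589 and state and justify the discordance of about 14% behind it.
4. Use the corrected figure as the reference for the interim decision on additional pairs.
5. If 15 points is the target and 5 points the conservative scenario, say so; the abstract's 15% can then stay.

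The cost is a change of wording and a less favourable stated number. Because the expected intervention group exceeds every figure in item 3 before clustering, neither recruitment nor data collection need change on this account.
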